## Abstract

**Background:**

Colorectal cancer (CRC) is a significant contributor to global mortality. However, the existing therapeutic approaches often fall short of achieving favorable outcomes especially in metastatic CRC. Brucea javanica Oil Emulsion Injection (BJOEI) as adjuvant therapy also showed superiority for cancer treatment in clinical practice. This trial aims to gather preliminary data to inform a phase III clinical trial evaluating the efficacy and safety of BJOEI in combination with best supportive care (BSC) for patients with advanced colorectal cancer who are refractory to all existing therapies.

**Methods:**

The study is designed as a multicenter, randomized, and controlled clinical trial. 60 eligible participants will be randomly assigned to the experimental or control group in a ratio of 1:1. The experimental group will receive BJOEI and BSC, while the control group will undergo BSC. The treatment will cease upon disease progression or when toxicity becomes intolerable. Follow-up assessments will be scheduled every 2 months, continuing until the patient dies, is lost to follow-up, or reaches 12 months post-randomization. The main outcome measured will be progression-free survival (PFS). Additional outcomes to be evaluated are clinical symptoms, quality of life, and overall survival (OS). Detailed records of adverse events (AEs) will be maintained.

**Expected outcomes:**

To the best of our knowledge, this is the first study to investigate the use of Traditional Chinese Medicine as a monotherapy in patients with advanced colorectal cancer who have failed multiple lines of standard treatment.

**Trial registration:**

Clinicaltrials.gov, NCT05897749. Registered on 09 May 2023.

## Introduction

Malignant tumors represent the second leading cause of global mortality, posing a paramount public health concern. According to the latest 2020 global cancer burden data released by the International Agency for Research on Cancer, there were 19.29 million newly diagnosed cancer cases and 9.96 million deaths worldwide in 2020. CRC accounted for 10% of the global cancer incidence and a mortality rate of 9%, highlighting a formidable challenge in the global landscape of cancer prevention and control (Sung et al., 2021). CRC, characterized by its heterogeneous nature, often arises from the intricate interplay of genetic and environmental factors. Current research emphasizes the role of mutations in APC, CHEK2, MLH1, MUTYH, and PTEN in increasing the risk of CRC (Seagle et al., 2023). Over half of the new cases may be linked to modifiable risk factors such as smoking, excessive alcohol consumption, antibiotic usage, sedentary lifestyle, and obesity (Zhou et al., 2023; Wu J. et al., 2023; Iwasaka et al., 2023; Zhai et al., 2023). Approximately 25% of all patients with CRC receive a diagnosis of metastatic CRC (mCRC), and 25%–30% of patients with an initial diagnosis of stage I–III CRC eventually develop mCRC within 5 years (Mousa et al., 2015; Cartwright, 2012; Shah et al., 2016; Arnold and Stein, 2013). The clinical treatment of CRC is mainly surgical treatment, while chemotherapy is a widely used adjuvant treatment for patients with middle-advanced CRC. According to the literature, approximately 80% of all recurrences manifest within the initial 3 years after surgery, with 95% occurring within 5 years (Sargent et al., 2009; Seo et al., 2013). Systemic therapy for metastatic colorectal cancer (mCRC) typically begins with chemotherapy regimens that combine a fluoropyrimidine with either oxaliplatin or irinotecan. Although immunotherapy shows potential for treating advanced CRC, it faces challenges such as immunotherapy resistance and a limited population of beneficiaries (Adebayo et al., 2023; Tan and Sahin, 2021). For mCRC that progresses despite these treatments, three oral drugs have been researched and approved: regorafenib (Grothey et al., 2013), fruquintinib (Dasari et al., 2023), and trifluridine/tipiracil (TAS-102) (Mayer et al., 2015). These medications are considered standard later-line treatments and have been shown to extend survival in patients with resistant mCRC. However, the benefits are not universal, as evidenced by the FRESCO study, which reported an objective response rate of only 4.7% for fruquintinib monotherapy.

Traditional Chinese medicine exhibits a range of pharmacological effects and plays a therapeutic role in many critical aspects of diseases. Brucea javanica, a medicinal plant found throughout Asia in open areas and secondary forests (Ye et al., 2015), has demonstrated significant potential in this regard. Extracts from its fruit have been shown to possess anti-proliferative and pro-apoptotic properties on human carcinoma cells (Man et al., 2012).BJOEI comprises oil-soluble components formulated into a water-in-oil emulsion with refined Brucea javanica, purified lecithin, glycerol, and injectable water. Widely employed as an anti-tumor Chinese herbal injection, BJOEI has obtained approval from the China Food and Drug Administration (China drug approval number: Z 19993152) for the treatment of lung cancer, brain metastases from lung cancer, and digestive system tumors. Recent studies investigated cytotoxicity effects of Brucea javanica on tumor such as lung (Xie et al., 2021), liver (Chen et al., 2016), colorectal (Bagheri et al., 2018a), gastric (Li et al., 2020), esophageal (Qiu et al., 2019), and pancreatic cancers (Wu Y. et al., 2023). Primarily, it initiates the activation of caspase-8/9 and concurrently modulates apoptosis-associated proteins. This coordinated modulation leads to the initiation of apoptotic pathways in HT29 and HCT116 CRC cells. Additionally, it exerts a direct inhibitory effect on HCT116 CRC cell proliferation by facilitating cellular autophagy (Bagheri et al., 2018a; Bagheri et al., 2018b; Yan et al., 2015). Besides, BJOEI as adjuvant therapy also showed superiority in efficacy and safety for cancer treatment in clinical practice (Chen et al., 2022). BJOEI plus chemoradiotherapy may have positive effects on lung cancer, gastric cancer and CRC (Nie et al., 2012; Wang et al., 2021; Gao and Zhang, 2023). It is very important to improve quality of life and reduce incidences of some adverse effects compared with chemoradiotherapy alone. This study is principally aimed at acquiring preliminary insights that will underpin a phase III clinical trial focused on the assessment of BJOEI’s efficacy and safety, administered in conjunction with optimal supportive care, for patients afflicted with mCRC who exhibit resistance to all prevailing therapeutic options.

## Methods

### Study objectives

The primary objective of this study is to gather preliminary data to inform a phase III clinical trial evaluating the efficacy and safety of BJOEI in combination with best supportive care for patients with advanced colorectal cancer who are refractory to all existing therapies.

### Study design

This study is a multicenter, randomized, and controlled clinical study comparing the efficacy and safety of BJOEI combined with BSC versus BSC in patients who are refractory to all available therapy. Eligible patients will be randomized in a 1:1 ratio to either the experimental group or the control group. Both groups will receive BSC in line with the NCCN palliative treatment guidelines (Dans et al., 2021). Participants assigned to the experimental group will be administered 30 mL of intravenous BJOEI daily for 1–14 days in each 28-day cycle. Conversely, the control group will receive only BSC. Treatment for eligible patients will continue until disease progression as defined by the Response Evaluation Criteria in Solid Tumors 1.1 (RECIST 1.1) (Eisenhauer et al., 2009), the onset of unacceptable toxicity, completion of 12 months from randomization, or withdrawal of informed consent. Follow-up evaluations will occur every 2 months until either death, loss of follow-up, or the 12-month mark from randomization. The trial has been registered on the Clinical Trials research platform (ClinicalTrials.gov, ID NCT05897749), and the participant timeline and trial flowchart are displayed in Figures 1, 2, respectively.

**FIGURE 1 F1:**
[figure not shown]
Participant timeline.

**FIGURE 2 F2:**
[figure not shown]
Trial flowchart.

### Ethics approval and patient consent

The study protocol has garnered approval from esteemed institutions, including the Guang’anmen Hospital of the China Academy of Chinese Medical Sciences, the First Affiliated Hospital of Guangzhou University of Chinese Medicine, Jiangsu Province Hospital of Chinese Medicine, Yueyang Hospital of Integrated Traditional Chinese and Western Medicine, and the Affiliated Hospital of Shandong University of Traditional Chinese Medicine. Informed consent from the candidates will be obtained by the study investigators at each participating center.

### Outcomes

#### Primary outcome

PFS: PFS is defined as the duration from randomization to the occurrence of tumor progression or death resulting from any cause, whichever transpires first.

#### Secondary outcomes

(1) Objective Response Rate (ORR): ORR represents the percentage of patients achieving a predefined reduction in tumor volume and maintaining this reduction for a specified minimum duration, assessed in accordance with RECIST 1.1 criteria.(2) OS: OS is the interval from randomization to death caused by any factor.(3) Quality of Life Assessment: The European Organization for Research and Treatment of Cancer Quality of Life Questionnaire-Core 30 (European Organisation for Research and Treatment of Cancer, 2001) and the Anderson Symptom Assessment Scale (Giesinger et al., 2021) will be employed to assess score changes.

#### Safety outcomes

We will adopt a more rigorous daily monitoring regime throughout the 14-day infusion cycles, incorporating vital signs monitoring, comprehensive clinical symptom assessment, and laboratory test. This enhanced monitoring approach will enable immediate detection and management of infusion-related adverse events, thereby improving patient safety during the most critical treatment periods. Any AEs that arise will be promptly documented, and the physician will provide treatment based on the specific circumstances. Serious AEs will be reported to the ethics committee. Insurance will cover any AEs resulting from the study.

### Eligibility criteria

#### Inclusion criteria

The participants who are included must meet all the following criteria:(1) Pathologically confirmed stage IV CRC patients who are refractory to all available therapy;(2) Individuals aged 18 to 75, regardless of gender;(3) Eastern Cooperative Oncology Group’s (ECOG) performance status is 0–2;(4) According to RECIST 1.1, at least one measurable target lesion;(5) Written informed consent obtained.

#### Exclusion criteria

Patients who meet one or more of the following criteria will be excluded:(1) Brain metastasis, the BRAF-V600E mutation, high microsatellite instability/deficient mismatch repair (MSI-H/dMMR), or NTRK fusion genes;(2) Patients with a history of other malignancies;(3) Previously recruited into another drug trial within the last 8 weeks.;(4) Severe disorders affecting the cardiovascular, cerebrovascular, hepatic, renal, or hematopoietic systems or those whose primary diseases are not effectively controlled;(5) Pregnant or lactating women, and women not using an effective form of contraception;(6) History of any hypersensitivity or allergic reaction to BJOEI.(7) Any condition (e.g. psychological, geographical, etc.) that does not permit compliance with the protocol.

### Randomization, allocation concealment and blinding

#### Randomization strategy

Participants will be randomly assigned to the control or experimental group in a 1:1 ratio using minimization randomization. Given our sample size of 60 patients, we implemented minimization rather than traditional stratified block randomization to ensure balanced allocation across multiple prognostic factors without creating formal strata that might have insufficient sample sizes. The minimization algorithm will consider three key factors: (1) primary tumor location (colon vs. rectal cancer), (2) ECOG performance status (0-1 vs. 2), and (3) study center. This approach is particularly suitable for smaller trials as it ensures balanced allocation across multiple factors while maintaining statistical efficiency.

#### Technical implementation

The randomization process will be overseen by an independent third-party statistical unit, specifically Beijing InnoTech Science & Technology Co., Ltd. A centralized web-based randomization system will implement the minimization algorithm using a computer-generated sequence with a random component (80% deterministic allocation based on minimization, 20% random allocation) to maintain unpredictability while achieving optimal balance. This ratio was selected to optimize both treatment balance and allocation concealment according to established recommendations for minimization algorithms in clinical trials.

#### Allocation concealment

Complete allocation concealment will be maintained through the centralized web-based system, which will only reveal treatment allocation after confirming patient eligibility and completing all required baseline assessments. The randomization sequence will be generated and stored securely by the independent statistical unit, ensuring that investigators and research personnel remain blinded to upcoming assignments throughout the enrollment process.

#### Blinding

This is an open-label study where neither participants nor treating physicians are blinded to treatment assignments due to the nature of the interventions. However, to minimize detection and measurement bias, several measures have been implemented for objective assessment of endpoints. Following CONSORT and SPIRIT guidelines, imaging studies for progression-free survival (PFS) will be centrally reviewed by two blinded board-certified radiologists who remain unaware of treatment assignments. Any discordant evaluations will be resolved by a third independent radiologist who is also blinded to treatment allocation. Quality-of-life assessments will be conducted and analyzed by study coordinators and an external data management team, both unaware of treatment assignments. These measures ensure that both objective and subjective endpoints are assessed impartially, minimizing detection and measurement bias despite the open-label nature of the study.

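### Masking coordinators and data managers cannot make quality-of-life scores impartial when the patients who give the answers know their allocation

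*Protocol article*

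**What the plan says.** All the statements are in the protocol article.

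- **Blinding**, on who knows the allocation: "neither participants nor treating physicians are blinded to treatment assignments due to the nature of the interventions".
- **Blinding**, on the protection offered for quality of life: "Quality-of-life assessments will be conducted and analyzed by study coordinators and an external data management team, both unaware of treatment assignments".
- **Blinding**, on what this achieves together with the masked radiology review: "These measures ensure that both objective and subjective endpoints are assessed impartially, minimizing detection and measurement bias despite the open-label nature of the study".
- **Secondary outcomes**, on the instruments: "The European Organization for Research and Treatment of Cancer Quality of Life Questionnaire-Core 30" and the Anderson symptom scale, which "will be employed to assess score changes".
- **Study design** and **Intervention**: the experimental arm has intravenous BJOEI daily on days 1–14 of each 28-day cycle in addition to best supportive care. The control arm has best supportive care alone.
- **Discussion**, limitations paragraph: a placebo is hard to obtain in China, so the study cannot be blinded. The paragraph does not mention quality of life in this connection.

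**The concern.** The Blinding section treats two kinds of endpoint alike. For progression on imaging, the radiologist's reading is the measurement, so a masked radiologist gives a masked measurement. For a questionnaire or a symptom scale, the patient's answer is the measurement. The people whom the section masks administer, handle or analyse that answer; they do not produce it. The person who does is described as unblinded at the start of the same section.

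What is at stake is how a quality-of-life difference will be read. Quality of life is a listed secondary outcome. The Introduction and Discussion cite quality-of-life benefit in support of BJOEI, mostly when it is added to chemotherapy or chemoradiotherapy. All tests are to be two-sided at 0.05, and the trial is meant to inform a phase III study. As the text stands, a between-arm difference would carry the protocol's own assurance of impartial measurement into that planning.

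**Working it through.** The plan gives no figure on this point, so there is none to reproduce. The check sets the statements side by side.

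**1. Who produces each measurement, and is that person masked?**

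| Endpoint | Who produces the value | Masked? |
|---|---|---|
| Progression on imaging | Two radiologists, with a third for discordant readings | Yes |
| EORTC QLQ-C30 | The patient, by answering a questionnaire | No |
| Anderson symptom scale | The patient, by rating symptoms | No |

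The article does not say whether forms are self-completed or taken at interview. It makes no difference here: either way the answer comes from the unblinded patient.

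**2. Could patients be unaware of their arm in practice?** No. One arm has daily infusions for 14 days of every 28, the other has none, and there is no placebo.

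**3. What can masking of coordinators and data managers do?** It can limit leading or prompting when forms are administered, and selective choices in data handling and analysis. It cannot change how a patient's knowledge of the allocation affects the answer.

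**4. Is the assurance withdrawn elsewhere?** No. The limitations paragraph concedes that blinding is impossible but does not apply this to quality of life.

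**5. Illustration of what an unremoved shift would do.** The documents give no size for response bias, so the shifts below are assumptions.

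Inputs: 30 per arm (Sample size), two-sided α = 0.05 (Statistical significance), no true effect, complete data, and a mean reporting shift of d standard deviations between arms. A normal approximation for comparing two means is used.

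- Standard error of the difference in SD units: √(2/30) = 0.258.
- P(p < 0.05) = [1 − Φ(1.96 − d/0.258)] + Φ(−1.96 − d/0.258).
- Worked case, d = 0.3: 0.3/0.258 = 1.16. The upper tail is 1 − Φ(0.80) = 0.212 and the lower tail is Φ(−3.12) = 0.001, a total of 0.213.

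| Assumed shift (SD) | Chance of p < 0.05 with no true effect |
|---|---|
| 0 | 5.0% |
| 0.1 | 6.7% |
| 0.2 | 12.1% |
| 0.3 | 21.3% |
| 0.5 | 49.1% |

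The table shows what a shift of a given size would do. It is no evidence that a shift of any given size will occur.

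**The case against.** The strongest reply is that the article is open about the design. It calls the trial open-label, lists the lack of blinding as its first limitation, says the study is not powered to test efficacy, and calls its findings hypothesis-generating. It speaks of minimizing bias, not eliminating it, and it nowhere claims that patients are masked. Quality of life is secondary, and the Discussion rests the evaluation on PFS.

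Much of this stands, and it keeps the point to one of wording and interpretation. It does not remove it. The sentence says that the measures ensure impartial assessment of subjective endpoints, which the stated design cannot deliver, and the general limitation is never connected to these scores.

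A reader might infer more than the documents support:

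- **That there is no protection at all.** This goes too far, because masked administration and analysis guard against prompting and selective analysis.
- **That the coordinators will in fact become unmasked.** The infusion schedule makes one wonder, but the article does not say where they work or what they see, and such operational detail may be in the full protocol.
- **That the bias must favour BJOEI.** Expectation could act that way, but 14 days of infusion and daily monitoring per cycle could also burden patients, and contact in the control arm is not described. Any effect of extra contact on how patients actually feel is also a different matter from measurement bias.
- **That the timing or manner of completing the forms is at fault.** The article does not describe it, the timeline figure is not shown, and a change of timing would not remove response bias from knowing the allocation.

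**Conclusion.** The point holds as a fault in a stated assurance. The Blinding section claims impartial assessment for endpoints whose values come from people it has just described as unblinded. The conclusion rests on one step that the article does not spell out: that a quality-of-life questionnaire and a symptom scale record the patient's own answers.

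The size and net direction of the response bias cannot be derived from the documents. The range of 5% to 49% depends wholly on assumed shifts of 0 to 0.5 SD and should not be cited as an estimate.

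The reach is limited to the two patient-reported instruments, both secondary, in a declared pilot. The masked central reading of scans for PFS is not touched by this point. The correction is still worth making, because it changes what a quality-of-life difference from this trial can be said to show.

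**What to change.** Three changes of text:

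1. In **Blinding**, limit the assurance of impartial assessment to the centrally read imaging. For quality of life, say that the scores are reported by unblinded patients and that only administration, data management and analysis are masked.
2. In **Statistical analysis**, say that between-arm differences in QLQ-C30 and symptom scores will be reported as descriptive and read as open to expectation bias.
3. In the limitations paragraph of the **Discussion**, connect the lack of blinding to the quality-of-life and symptom outcomes explicitly.

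The cost is a weaker quality-of-life claim. No extra staff, visits or procedures are needed, and the sample size and the PFS analysis stay as they are.

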### Intervention

#### Control group: BSC

BSC is defined as those measures designed to provide palliation of symptoms and improve quality of life as much as possible. All patients will receive BSC based on the NCCN Palliative Treatment Guidelines (Dans et al., 2021).

#### Experimental group: BJOEI, in addition to the BSC

Participants in the experimental group will receive intravenous BJOEI 30 mL per day continuously for 1–14 days of a 28-day cycle.

Both groups will undergo corresponding interventions until disease progression, death, the occurrence of unacceptable toxic effects, withdrawal of consent by the patient, or a decision by the treating physician to discontinue the intervention in the patient’s best interest.

BJOEI (specifications:10mL/tube) will be manufactured by Jiangsu Jiuxu Pharmaceutical Co. Ltd. (Xuzhou, China).

#### Sample size

Many patients experience rapid disease progression with third- and fourth-line therapies, leaving them with limited therapeutic options. BJOEI has shown potential benefits for these patients.As an external pilot RCT, this study is not powered to test efficacy. A total of 60 participants (30 per arm) was selected to provide adequate precision for estimates of median PFS and variance while remaining logistically feasible. This aligns with published recommendations (15–25 per arm) and will inform the definitive phase III sample-size calculation (Sim and Lewis, 2012; Whitehead et al., 2016).

